## Methods and analysis

### Study design

To address objective 1, we will conduct a single-centre, 36-month, prospective cohort study in 800 HIV-infected patients initiating ART and 190 HIV-uninfected adults aged ≥35 years. HIV-infected and HIV-uninfected participants will be frequency-matched by 5-year age band and sex. On a 6-monthly basis, we will measure markers of viral infection, inflammation and endothelial function along with surrogate markers for CBD/CVD (table 1).

**Table 1 T1:** Laboratory tests and clinical procedures in ART patients and HIV-uninfected adults

	Study time points						
	Baseline	6 months	12 months	18 months	24 months	30 months	36 months
Clinical procedures							
PWV	X	X	X	X	X	X	X
CIMT	X				X		
ABPI	X	X	X	X	X	X	X
Cardiac echo (participant subset)	X				X		
ECG (participant subset)	X				X		
Cardiometabolic markers							
Creatinine Full blood count	X X	X			X		
Cholesterol (LDL, HDL, triglycerides)	X				X		
Serum glucose/haemoglobin A1c	X				X		
HIV infection and progression							
HIV viral load (patients with HIV)	X	X	X				
CD4 count (patients with HIV)	X	X	X				
HIV rapid test (controls)	X		X		X		X
Immune dysregulation							
Soluble markers of systemic inflammation	X	X	X				
Soluble markers of endothelial activation	X	X	X				
CD8 and CD4 T cell activation and senescence (participant subset)	X	X	X		X		X
Monocyte/Macrophage activation and senescence (participant subset)	X	X	X		X		X
Herpesviruses infection							
CMV IgG	X	X					
VZV IgG	X	X					

ABPI, Ankle Brachial Pressure Index; ART, antiretroviral therapy; CIMT, carotid intima-media thickness; CMV, cytomegalovirus; HDL, high-density lipoprotein; LDL, low-density lipoprotein; PWV, pulse wave velocity; VZV, varicella zoster virus.

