### Study participants

Study inclusion criteria will be (1) age ≥35 years and (2) resident of Blantyre. HIV-infected patients must further be (3) ART-naïve or initiated ART <10 days prior to enrolment and (4) initiating standard first-line ART. Adult controls must further be (5) HIV-uninfected. Study exclusion criteria are (6) clinical history of CBD/CVD, (7) pregnancy, (8) critical illness or symptomatic anaemia at baseline, and (9) enrolment in an intervention study. At the analysis stage abnormal pulse wave velocity (PWV) at baseline (as defined in table 2) will be excluded for new-onset vasculopathy analysis but not for progression of vasculopathy. The same approach will be applied for baseline carotid intima-media thickness (CIMT) measurements. If the study participant becomes pregnant after recruitment, they will be withdrawn.

**Table 2 T2:** Case definitions of primary and secondary endpoints for the study

Type	Definitions
Primary endpoint	Carotid intima-media thickness (CIMT)	*The occurrence of new-onset vasculopathy**(**CIMT, a measure of atherosclerosis**)*: CIMT >0.9 mm or >75th percentile of age/sex references values or presence of plaque on the carotid scan. *Progression*: total change in CIMT at 24 months from baseline.
	Pulse wave velocity (PWV)	*Occurrence of new-onset vasculopathy**(**PWV*,*a measure of arterial stiffness**)*: PWV >12 (m/s). *Progression*: total change in PWV at 24 months from baseline.
Secondary endpoint	Stroke	*Confirmed (**1**+**2**) or 3 or 4 or 5:* Acute onset with a clinically compatible course, including unequivocal objective findings of a localising neurological deficit. CT or MRI compatible with a diagnosis of stroke and current neurological signs and symptoms. Stroke diagnosed as the cause of death at autopsy. Clinical history and positive lumbar puncture compatible with subarachnoid haemorrhage. Death certificate or death note from medical record listing stroke as the cause of death.

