	Myocardial infarction (MI	*Confirmed:**o**ne of the following**five**criteria (adapted from**2007**Universal Definition of**Myocardial Infarction**)**(**1 + (2 or 3**or 6))**or 4 or 5*: Rise and/or fall of cardiac biomarkers (preferably troponin), with at least one value above the 99th percentile of the upper reference limit. The occurrence of a compatible clinical syndrome, including symptoms consistent with myocardial ischaemia. ECG changes indicative of new ischaemia (new ST changes or new left bundle branch block (LBBB)), or development of pathological Q waves on the ECG. Sudden unexpected cardiac death involving cardiac arrest before biomarkers are obtained or before a time when biomarkers appear, along with (a) new ST changes or new LBBB, or (b) evidence of fresh thrombus on coronary angiography or at autopsy. Pathological findings of acute MI (including acute MI demonstrated as the cause of death on autopsy). Development of (a) evolving new Q waves or (b) evolving ST elevation, preferably based on at least 2 ECGs taken during the same hospital admission.
	Coronary artery disease requiring drug treatment	*Confirmed (**1**or 2)**+**3*: Evidence of myocardial ischaemia based on either diagnostic imaging (such as a stress echocardiogram or thallium scan) or diagnostic changes on an ECG (such as during stress testing or an episode of chest pain). Evidence of coronary artery disease based on coronary angiography or other diagnostic imaging. Use of medication given to treat or prevent angina (eg, nitrates, beta blockers, calcium channel blockers).
	Peripheral vascular disease	*Confirmed (**1**+**2**) or (**1**+**3**)*: Compatible clinical signs and symptoms. Positive results on diagnostic imaging studies (eg, Doppler ultrasound, contrast arteriography, MRI arteriography). Ankle brachial pressure index <0.90 in non-diabetics.
	Vascular Immune reconstitutionsyndrome (IRIS)	A new onset vasculopathy within 6 months of starting ART
	All-cause death and vascular-related deaths	Death (of any or vascular cause) that occurs after recruitment into the study.

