### Secondary outcomes

The secondary outcomes are the following clinical events: (1) stroke, (2) MI, (3) unstable angina, (4) PVD, (5) all-cause death/vascular death and (6) immune reconstitution inflammatory syndrome (IRIS) vasculopathy (table 2). Changes in PWV or endothelial activation at 6 months post-ART initiation will be interpreted as a subclinical vascular IRIS event. These outcomes will be assessed through active surveillance in QECH inpatient wards for admissions of study participants. To improve capture of clinical outcomes, we will conduct brief telephone interviews with study participants about CBD/CVD symptoms and hospitalisations between study visits and facilitate unsolicited participant self-report. Clinical events and deaths in study participants will be reviewed by an independent endpoint review committee (ERC), comprising clinicians experienced in endpoint review. Each event will be reviewed and adjudicated by the ERC chair and two ERC reviewers, using a standard set of diagnostic criteria (table 2 and online supplementary S1). The format of reporting will be based on modifications of the INSIGHT network clinical diagnostic criteria. Deaths will be reviewed by the ERC using the International Classification of Diseases for causes of death classificaton.^23^ For death with limited clinical data, a validated verbal autopsy will be performed to ascertain the cause.^38^

10.1136/bmjopen-2018-025576.supp1Supplementary data

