### Sample size and statistical analysis

The required sample size for the study’s primary objectives is 800 HIV-infected patients and 190 HIV-uninfected adults using standard, normal distribution approximation sample size formulas for comparing proportions in two groups of unequal size and based on the following assumptions: (1) of HIV-infected study participants, 18.4% have abnormal PWV at baseline. We will exclude these participants from analysis. The 18.4% figure is informed by our ongoing studies of vasculopathy in HIV-infected patients, where this is the percentage of participants aged ≥35 years who have a PWV (>12 m/s). (2) Of both HIV-infected patients and HIV-uninfected adults, 20% will be lost to follow-up, including by death and HIV seroconversion.^40 41^ (3) The minimum relative risk (RR) of interest is 2 for objective 1 and 1.8 for objective 2. (4) The 24-month cumulative risk of clinically significant vasculopathy over study follow-up is 18.4% in the HIV-positive group. This is based on the same study data cited in (1). (5) For objectives 2a–2c, the exposure prevalence for each risk factor is 20%. (6) Statistical tests will have 80% power based on a two-sided test with α=0.05. Testing of hypotheses for the secondary outcome will be exploratory. However, we estimate 26 strokes (4 mimics), an unknown number of MIs and 80 deaths occurring during the study.^7 42^ Taken together, assumptions (3), (4) and (5) mean that, for 80% power, we assume a 24-month cumulative vasculopathy risk of 9.2% in HIV-negative participants, 18.4% in all HIV-infected participants, 15.9% in HIV-infected participants not exposed to the risk factors from objectives 2a–2c and 28.6% in the HIV-infected participants exposed to these risk factors.

The reporting of this study will be prepared in accordance with the Strengthening the Reporting of Observational Studies in Epidemiology guidelines.^43^ Summary and descriptive statistics will be tabulated for all primary and secondary outcome variables, as well as for exposure variables and potential confounding or mediating factors. Time plots for all outcome variables will be inspected. Quantitative data analysis will be conducted to assess the primary outcomes.

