There will be three analysis time points: (1) after recruitment has finished and baseline data are available for all participants (baseline analysis); (2) once every participant has completed 6 months in the study (6-month analysis); and (3) at 36 months, when each participant has completed 24 months in the study (final analysis).

The baseline analysis will largely consist of descriptive statistics on participant characteristics and data recorded at baseline. Simple regression models will also be used to investigate relationships between exposure and outcome variables measured at baseline. Unadjusted analyses will consist of paired t-tests or Wilcoxon signed-rank tests (depending on whether the data are normally distributed or not) for continuously measured variables, and χ^2^ or Fisher’s exact tests (depending on contingency table cell counts) for binary and categorical variables. Adjusted analyses will be conducted using generalised linear models (GLMs).

The 6-month analysis will be limited in scope and serves two purposes: (1) characterise new-onset vasculopathy in HIV-infected participants who have initiated ART treatment at baseline (vascular IRIS) and (2) define vasculopathy outcomes for the final analysis. The main analysis of the study data will be conducted at the final analysis time point.

For objective 1 we will develop three regression models. Two GLMs will be developed to compare mean progression of arterial damage from baseline in HIV-infected ART patients and HIV-uninfected adults. These models will regress change from baseline PWV and CIMT, respectively, on HIV status. We will develop a third model to estimate the RR and population-attributable fraction of new-onset arterial damage in HIV-infected patients compared with HIV-uninfected adults.

For objective 2a, a set of GLMs will be developed to compare mean progression of vasculopathy in HIV-infected ART patients with and without reactivated latent herpes viral infection. These models will regress PWV and CIMT, respectively, on, on two log-transformed variables for antibody titres of CMV and VZV.

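### Vascular IRIS is defined by timing alone and described at 6 months in HIV-infected patients only, so an unknown share of the labelled events will be background that the control data could show

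*Protocol article*

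**What the plan says.** Table 2 of the protocol article (under Study participants) defines vascular IRIS as "A new onset vasculopathy within 6 months of starting ART". This is a definition by timing. It names no comparator and no criterion that links the event to immune reconstitution. Secondary outcomes adds a subclinical form: "Changes in PWV or endothelial activation at 6 months post-ART initiation will be interpreted as a subclinical vascular IRIS event". It gives no size, direction or reference group for the change.

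Sample size and statistical analysis describes the 6-month analysis as limited in scope, with two purposes. One is to "characterise new-onset vasculopathy in HIV-infected participants who have initiated ART treatment at baseline (vascular IRIS"). The other is to settle the vasculopathy outcomes for the final analysis. The first purpose names HIV-infected participants only.

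The measurements cover both groups. Table 1 is titled "Laboratory tests and clinical procedures in ART patients and HIV-uninfected adults". It marks PWV at baseline and at every 6-monthly visit, and soluble endothelial markers at baseline, 6 and 12 months. Neither row is restricted to patients with HIV, whereas the viral load and CD4 rows are. Carotid intima-media thickness (CIMT) is marked at baseline and 24 months only. Participants with abnormal baseline PWV (above 12 m/s) "will be excluded for new-onset vasculopathy analysis but not for progression of vasculopathy".

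The sample size section expects vasculopathy in controls too: "we assume a 24-month cumulative vasculopathy risk of 9.2% in HIV-negative participants, 18.4% in all HIV-infected participants".

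The status of vascular IRIS is inconsistent. Study objectives, Table 2 and Secondary outcomes list it as secondary, while the Exposures section says it will be treated as a primary endpoint.

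**The concern.** Some people with PWV at or below 12 m/s at baseline will be above it six months later whatever their HIV or ART status, through ageing, blood pressure or measurement variation near the threshold. The stated rule calls every such crossing in an ART initiator vascular IRIS. The subclinical rule goes further and fixes in advance how any 6-month change is to be read.

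A count in one group cannot show how much of it is background. A reader of the 6-month report could take the whole count as a vascular effect of immune reconstitution. The stakes rise if the endpoint is treated as primary, as one section says, and because the same analysis is to settle outcome definitions for the final analysis.

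**Working it through.** **The plan's own figures.** The control risk is the HIV-infected risk divided by the minimum relative risk of interest: 18.4% / 2 = 9.2%. It is a design assumption and not an observed rate. With 800 x 0.816 x 0.8 = 522 evaluable patients and 190 x 0.8 = 152 controls, a normal-approximation comparison of 18.4% with 9.2% (two-sided alpha 0.05) has 80.8% power. This agrees with the stated 80%.

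**Six-month risks (assumption).** The article gives no 6-month risk, so the 24-month risks are scaled in two ways.
- Constant hazard, 1 - (1 - p)^(6/24): controls 1 - 0.908^0.25 = 2.4%; HIV-infected 1 - 0.816^0.25 = 5.0%.
- Even accrual, p/4: controls 2.3%; HIV-infected 4.6%.

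**Events that would carry the label.** Patients with normal baseline PWV: 800 x 0.816 = 653.
- Constant hazard: 653 x 0.0496 = 32 labelled; 653 x 0.0238 = 16 expected at the control rate (48%).
- Even accrual: 653 x 0.046 = 30 labelled; 653 x 0.023 = 15 expected at the control rate (50%).
- With the full 20% loss already applied (522 patients), constant hazard: 26 and 12.

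Neither scaling contains any early ART-specific effect, yet about 30-32 events would be labelled.

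**How far the share can be trusted.** The background share is the control risk divided by the patient risk, which is 1/RR. The value near one half therefore restates the assumed RR of 2. Holding the control risk at 2.38% and varying the true excess:
- no excess: 100%
- excess of 2 points: 2.38 / 4.38 = 54%
- excess of 5 points: 2.38 / 7.38 = 32%

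**Precision of a two-group comparison.** The assumed difference is 4.96 - 2.38 = 2.6 points. SE = sqrt[0.0238 x 0.9762 / n + 0.0496 x 0.9504 / 653], where n is the number of controls.
- n = 190: SE 1.40 points; 95% CI half-width 2.7 points; power about 30%.
- n = 190 x 0.816 = 155 (if controls had the same baseline exclusion): SE 1.49 points; half-width 2.9 points; power about 24%.

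**The case against.** There are four serious points on the other side.

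First, a reader might infer that the control measurements are collected and never used. That is not so. Objective 1 regresses change in PWV on HIV status and estimates the relative risk of new-onset damage against controls. The PWV models are then extended to mixed models that take in the repeated measurements, including month 6. This stands. What remains is that nothing ties that contrast to the 6-month event or the IRIS label.

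Second, the secondary objective has an internal comparison: events are to be tabulated within exposure strata and, if numbers allow, modelled between them. Background crossings unrelated to exposure would tend to dilute such a ratio and not create one. This also stands. It does not give the background rate, since the event is timed from ART start and controls cannot meet it.

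Third, the 6-month analysis is descriptive, and testing of secondary outcomes is exploratory. A reader might infer that the study will report a spurious ART effect. The article plans no effect estimate or test at that point, so the fault lies in the label and the announced interpretation. The text does fix both of these; neither is detail left to a document not shown.

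Fourth, controls differ from patients in HIV as well as ART. An excess over controls would mix the two, and the article concedes that the lack of an ART-naïve group limits what can be said about ART. This stands and restricts what the remedy can claim.

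**Conclusion.** The point holds as one of labelling and reporting. Following the stated rules, background new-onset vasculopathy and re-measurement noise in ART initiators would be called vascular IRIS, although a matched group is measured at the same visits. This needs only a background rate above zero, which the plan itself assumes.

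The size is not known. It is tempting to say that half the events would be background, but the documents do not support this as a finding. The figure follows from the assumed RR of 2 and an assumed constant hazard or even accrual.

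Nor can the excess over controls be read as IRIS. Under the constant-hazard illustration, about 16 of the 32 events exceed the control rate with no ART-specific effect built in. The comparison would account for ageing, drift and threshold noise, and would leave HIV and ART together.

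**What to change.** 1. In the 6-month analysis, apply the identical rule (baseline PWV at or below 12 m/s, 6-month PWV above 12 m/s) to both groups. Report both risks and the age- and sex-adjusted risk difference with a 95% CI.
2. Compare the 6-month changes in PWV and in soluble endothelial markers between groups in the same way.
3. Name the event new-onset vasculopathy in the first 6 months of ART. In Secondary outcomes, replace the announced interpretation with a statement that an excess over controls is consistent with vascular IRIS but does not establish it, because HIV and ART cannot be separated.
4. State in Table 2 that the 6-month surrogate event rests on PWV, since CIMT is not measured at that visit.
5. Reconcile the primary status in Exposures with the secondary status in Study objectives, Table 2 and Secondary outcomes.

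The cost is wording and one comparison on data already scheduled. The drawback is precision: with at most 190 controls, the CI half-width is about as large as the assumed difference. The comparison should be presented as descriptive, and an interval that includes zero should not be read as absence of an effect.

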### Study objectives

This study will test the hypothesis that immune activation and dysfunction, driven by HIV and reactivation of latent CMV/VZV herpesvirus infections, lead to increased CBD/CVD risk in adults aged ≥35 years in SSA. We will address this through the following objectives:

To determine if progression of the surrogate marker of CBD/CVD or occurrence of new-onset vasculopathy is higher in adults aged ≥35 years with HIV infection on ART compared with those without HIV.To determine if progression of surrogate markers of CBD/CVD or occurrence of new-onset vasculopathy is higher in adults aged ≥35 years with HIV/herpes viral antigenaemia or chronic immune activation compared with those without HIV/herpes viral antigenaemia or chronic immune activation. Specifically, we will determine if progression of surrogate markers or new-onset vasculopathy is higher in the following:In ART patients with reactivated latent herpes viral infection, compared with those without reactivated latent herpes viral infection.In ART patients with the highest 25% of markers for immune activation, inflammation or endothelial activation compared with the bottom 25%.In ART patients with incomplete virological suppression or virological resurgence of HIV, compared with those with suppressed HIV plasma viral load.

The secondary study objectives are to determine if viral antigenaemia or chronic immune activation increases the occurrence of the following clinical events: (1) stroke, (2) MI, (3) angina (excluding MI), (4) peripheral vascular disease (PVD), (5) all-cause death/vascular-related death and (6) immune reconstitution inflammatory vasculopathy.

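### Excluding PWV above 12 m/s at baseline does not equalise the groups: if fewer controls than HIV patients are abnormal at baseline, the objective 1 new-onset RR mixes earlier PWV level with new damage

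*Protocol article*

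**What the plan says.** Objective 1 (Study objectives) asks whether progression of the surrogate marker "or occurrence of new-onset vasculopathy is higher in adults aged ≥35 years with HIV infection on ART compared with those without HIV". Table 2 defines new-onset PWV vasculopathy as a value above 12 m/s.

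Baseline abnormality is handled by exclusion. Study participants states: "At the analysis stage abnormal pulse wave velocity (PWV) at baseline (as defined in table 2) will be excluded for new-onset vasculopathy analysis". No group is named, so the rule reads as covering both. The only baseline share given is for patients: "of HIV-infected study participants, 18.4% have abnormal PWV at baseline. We will exclude these participants from analysis" (Sample size and statistical analysis).

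Two of the objective 1 models regress change from baseline in PWV and CIMT on HIV status. The third is described as follows: "We will develop a third model to estimate the RR and population-attributable fraction of new-onset arterial damage in HIV-infected patients compared with HIV-uninfected adults". Its terms are not listed. Matching is by 5-year age band and sex. The abstract promises multivariable models, and the Exposures section lists confounding and mediating factors to be recorded. Baseline PWV is not in that list, and adjustment for it is mentioned nowhere.

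**The concern.** Cutting two shifted distributions at the same value leaves them shifted. If patients have more PWV values above 12 m/s at baseline than controls, the patients who remain below 12 m/s will also tend to sit nearer to it. An equal true rise then carries more of them over the line. The new-onset RR would exceed 1 although nothing progressed faster on ART. This arises even with error-free readings, so repeating the measurement would not cure it.

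New-onset vasculopathy is a primary outcome. The RR also feeds a population-attributable fraction, which is meaningful for new damage only if the RR reflects new damage. A difference already present when ART started could be reported as damage arising on ART, at a size not far from the minimum RR of interest, 2.

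**Working it through.** **Inputs from the protocol article (Sample size and statistical analysis).** 800 patients and 190 controls; 18.4% of patients abnormal at baseline; 20% loss in both groups; 24-month risk 18.4% in patients and 9.2% in controls; two-sided α 0.05, 80% power.

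**Not in the article, so assumed and varied.** The share of controls abnormal at baseline, and the SD, correlation and progression of PWV. PWV is taken as normal with equal SD in both groups.

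**Step 1: the plan's own figure.** Evaluable patients: 800 × 0.816 × 0.8 = 522. Evaluable controls: 190 × 0.8 = 152. With the pooled test, power = Φ[(difference − 1.96·SE₀)/SE₁]. Here SE₀ = √[0.1633 × 0.8367 × (1/522 + 1/152)] = 0.0341 and SE₁ = √[0.184 × 0.816/522 + 0.092 × 0.908/152] = 0.0289. Power = Φ[(0.092 − 0.0668)/0.0289] = Φ(0.87) ≈ 81%. The figure reproduces, but with no control removed for abnormal PWV. Removing 9.2% of controls leaves 152 × 0.908 = 138 and gives 77.3%.

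**Step 2: the RR under identical progression.** Put the cut-off at 0 and the baseline SD at 1. Everyone rises by the same d, chosen so that 18.4% of baseline-normal patients cross.

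- Patients: the baseline cut-off lies z(0.184) = 0.900 SD above the mean. The share above it at 24 months is 0.184 + 0.816 × 0.184 = 0.334, with z = 0.428. So d = 0.900 − 0.428 = 0.472.
- Controls, if 9.2% are abnormal: z = 1.329, and 1.329 − 0.472 = 0.857, so 19.6% are above at 24 months. New onset = (0.1958 − 0.092)/0.908 = 11.4%. RR = 0.184/0.1143 = 1.61.
- Controls, if 12%: (0.2409 − 0.12)/0.88 = 13.7%, RR 1.34.
- Controls, if 15%: (0.2861 − 0.15)/0.85 = 16.0%, RR 1.15.
- Controls, if 22%: (0.3819 − 0.22)/0.78 = 20.8%, RR 0.89.

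**Step 3: other assumptions.** Model A lets individual true change vary, with SD 0 to 0.4 baseline SDs. Model B takes baseline and 24-month PWV as bivariate normal with equal SD at both times (1.5-2.5 m/s), correlation 0.5-0.95 and a common drift. Both keep patient new onset at 18.4%.

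| Controls abnormal at baseline (assumed) | RR, model A | RR, model B | Gap in mean baseline PWV after exclusion (SD 2 m/s) | Rejection rate, test without baseline PWV (model A) |
|---|---|---|---|---|
| 9.2% | 1.50-1.61 | 1.61-1.77 | 0.57 m/s | 39-49% |
| 12% | 1.28-1.34 | 1.34-1.42 | 0.35 m/s | 18-23% |
| 15% | 1.13-1.15 | 1.15-1.18 | 0.17 m/s | 8-9% |
| 18.4% | 1.00 | 1.00 | 0 | 5% |
| 22% | 0.89-0.90 | not run | not run | not run |
| 25% | 0.81-0.84 | not run | not run | not run |

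**Step 4: the attributable fraction.** Among the exposed it is (RR − 1)/RR. An RR of 1.5 gives 0.5/1.5 = 33%, and 1.8 gives 0.8/1.8 = 44%. For illustration, at the roughly 10% adult HIV prevalence in the Introduction the population fraction is 0.05/1.05 = 4.8% or 0.08/1.08 = 7.4%. All of it would be spurious as a measure of new damage.

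**Step 5: what adjustment does.** In 1,000 simulated trials with error-free readings and 9.2% of controls abnormal (640 v 152 before exclusion; SD of change 0.2, 0.4, 0.6), modified Poisson without baseline PWV rejected 44%, 38% and 31% of the time. With baseline PWV it rejected 4.5%, 4.1% and 4.3%, median RR 1.00. When PWV is read with error the bias shrinks but stays: crude 1.60-1.71, adjusted 1.09-1.28.

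**The case against.** **No control baseline PWV is given.** A reader might infer that controls do start further below 12 m/s and that the model will return a false RR of 1.5-1.6. The article does not support that. The 9.2% is its 24-month control risk, carried over here to baseline, and the bias vanishes or reverses if controls are equally or more abnormal. This stands, so the point is conditional. A gap in the stated direction is still the expected case: the hypothesis is that HIV drives vasculopathy, and patients enter ART-naïve or within 10 days of starting, after a period of untreated infection. That the sample size removes no controls is compatible with this but proves nothing about their PWV.

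**Silence is not an unadjusted analysis.** A reader might infer that HIV status is the only term in the third model. The wording about regressing on HIV status belongs to the two change models, and a covariate list may sit in an analysis plan that is not shown. This stands too, so the missing list is not the error. What remains is that the one stated device for baseline PWV, exclusion at the cut-off, does not do this job, and the recorded confounders do not include baseline PWV.

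**The RR is true for occurrence.** If patients cross 12 m/s more often, their incidence by Table 2 is higher, and a test of equal occurrence keeps its 5% level. The change-from-baseline models and their mixed-model extension address progression. This is correct. The rejection rates above apply only when the result is read as evidence of faster new damage, and to a test without baseline PWV. The reading as new damage is nevertheless invited by the article's term new-onset arterial damage and by the attributable fraction.

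**Adjustment is contestable.** HIV infection precedes baseline, so baseline PWV may carry part of its effect. This stands and is why both RRs should be shown.

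**Conclusion.** The point holds in conditional form. Exclusion at 12 m/s does not equalise baseline PWV. If fewer controls than patients are abnormal at baseline, an RR that ignores starting PWV mixes earlier level with new damage. Under identical progression its size is about 1.1-1.2 at 15% of controls abnormal, 1.3-1.4 at 12% and 1.5-1.8 at 9.2%; it is 1.0 at 18.4% and below 1 above that.

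These figures rest on normal PWV with equal SD, equal progression in both groups, 18.4% new onset in patients, and control shares that are assumptions throughout. The direction needs only that controls be less often abnormal at baseline.

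Two extensions are not established. New-onset CIMT has the same exclusion rule, so the logic may apply, but its definition is composite (thickness, age/sex percentile or plaque) and it was not quantified. One might also argue that unequal exclusion disturbs the age match; that is plausible, but no figure supports it.

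**What to change.** In the description of the third objective 1 model, prespecify an RR for new-onset PWV adjusted for continuous baseline PWV, 5-year age band and sex, for example by modified Poisson regression with robust standard errors. Report it beside the RR not adjusted for baseline PWV. Base any claim of excess new damage on ART, and the attributable fraction that goes with it, on the baseline-adjusted RR. Tabulate baseline PWV by group before and after the exclusion, so that a reader can see whether a gap exists. Consider whether new-onset CIMT needs the same treatment.

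State two limits. The adjusted RR is conditional on starting PWV, so it leaves out HIV effects accrued before ART. Measurement error in baseline PWV leaves some residual bias (1.09-1.28 in the simulations above).

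The cost is a few sentences and no new data, since baseline PWV, age and sex are already collected. If the groups prove alike at baseline, little is lost.
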